## Abstract

**Objective:**

In sub Saharan Africa one of the key challenges in assessment using neuropsychological tools has been the lack of adequately validated and easily implementable measures. This study will translate into English, adapt and standardize the Computerized Battery for Neuropsychological Evaluation of Children (BENCI). The BENCI battery will be adapted using back-translation design, comprehensive cultural adaptation and standardized in a case–control study involving two groups of children: HIV infected and HIV unexposed, uninfected children. The content adaptation will be iteratively carried out using knowledge of English and feedback from pilot testing with children. The proposed study will first involve the cultural adaptation of the BENCI. It will then recruit 544 children aged 8–11 years with half of them being HIV+, while the other half will be HIV unexposed-uninfected. Test–retest reliability will be analyzed using Pearson’s correlation while ANOVA and correlational analyses will be used to calculate discriminant, convergent and construct validity.

**Results:**

This study will result in an open access adequately adapted and standardized measure of neuropsychological functioning for use with children in East Africa. The protocol paper provides an opportunity to share the planned methods and approaches.

## Introduction

Children growing up in low and middle-income countries (LAMICs) are at a significant risk of experiencing neurocognitive impairment due to exposure to multiple risk factors [1]. However, the true burden of neurocognitive impairment is not documented largely due to a shortage of adequately standardized, easy to implement measures within these contexts [2, 3]. While a host of neuropsychological tools are currently available, unfortunately, they are not widely tested in African settings due to resource limitations. There is evidence to indicate that importing western measures into LAMICs without adequate attention to adaptation, standardization and validation can contribute to significant challenges in the validity of the data.

Recent efforts indicate that using systematic adaptation process can contribute to the development of neuropsychological measures that can be adequately used in LAMICs settings [4]. We would like to contribute to the body of literature by translating, adapting and providing validity data for the English version of The Computerized Battery for Neuropsychological Evaluation of Children (BENCI). BENCI is a neuropsychological tool originally developed and standardized in Spanish. It aims to capture diverse cognitive functions [5]. Some of the key neuropsychological domains assessed by BENCI include executive functioning, attention, processing speed, language, visual and verbal memory, and visuo-motor coordination.

One attractive feature of the BENCI is its computerized nature which makes it relatively easy to administer and get results readily and paper-free. The BENCI has good psychometric properties in terms of validity and reliability [5]. It has demonstrated good discriminant and construct validity, as well as test retest reliability in Morocco [5] and Ecuador [6]. The battery is relatively easy to administer as there are trial tests in between the subtests. These properties of the BENCI make it favorable for adaptation and standardization in the Kenyan children population. Earlier studies such as those by Holding and colleagues indicated there was a need to have sufficient trials for children in our settings [7]. In addition, BENCI is attractive since it is an open access tool for all mental health professionals particularly those who work in LAMIC will find it very beneficial as it was developed specifically for such contexts and there is no fee tied to its use.

The general objective of this study is to establish the reliability and validity of the BENCI and its utility in monitoring outcomes among HIV positive school going children. The specific objectives are:To evaluate the internal consistency, and re-test reliability of the BENCI;To evaluate the construct and criterion validity of these measures;To evaluate discriminative validity of the measures by comparing the performance of HIV infected and HIV exposed uninfected school going children.

## Main text

### Methods

#### Design

A three-phased approach will be carried out. In the first phase, the linguistic and semantic equivalence of the BENCI content will be ensured through back translation design from Spanish to English by two translators. An evaluation of the tools structure and appropriateness will also be done where psychologists will check for the appropriateness of the pictures and other materials. In the second phase, a pilot study among 10 children will evaluate the appropriateness of the items including pictures and instructions. While in the third phase, the psychometric properties of the English version of the BENCI with regards to the Kenyan population of HIV+ children will be evaluated in a case control study at a HIV programme and three public schools.

#### Study settings

One of the study sites will be a county level HIV programme, which is an outpatient programme catering for HIV infected individuals and their families from culturally diverse backgrounds within resource poor settings.

The normative data will be collected from 3 primary schools in the resource poor setting in Nairobi County.

The two settings are in the Kenyan capital city of Nairobi which has a high level of literacy (87.1%) with English being the primary language of instruction in the schools [8]. An English version of the BENCI is therefore ideal for adaptation. We will ensure that the level of English being used is basic and understand to the target population by pilot testing.

#### Instruments description

A socio-demographic questionnaire will incorporate elements such as age, gender and education background among other variables.

A breakdown of measures within each cognitive domain within BENCI is available in Table 1. The BENCI battery was developed using neuropsychological procedures that are valid with regards to the neuropsychological assessment literature which includes DSM V preferred domain assessments [9]. The test has norms for children aged 6–11 years. The test can be administered within 75 min with a 10-min break in between the 14 neuropsychological tests as shown in Fig. 1.

**Table 1 Tab1:** Comparison of domains and tests used in each domain

BENCI (90 min)		Kilifi Toolkit (120 min)	
Domain	Test	Domain	Test
Processing speed	Simple reaction time test (a plus sign of the screen prompts the child to press a key on the keyboard fast)	–	–
Visuo-motor coordination	Visuo-motor test (involves connection of elements/number in a given sequence)	Verbal/visual selective reminding	Self-ordered pointing test—SOPT (Selection of pictures displayed in varying positions on separate sheets in sets of 6, 8, 10, and 12. As each page is turned the subject is required to identify all members of the set, but to point to each item of the set only once. Touching a picture more than once is considered an error)
Sustained attention	Continuous performance test (respondent presses any key every time the required stimulus appears)	Auditory sustained and selective attention Visual sustained and selective attention	Score (the subject is required to place beads on one of two plates only after a special sound is heard on a cassette tape) People search (a stimulus sheet comprising complete and incomplete stick figures is presented. The subject is required to cross out only complete figures, as quickly as possible)
Memory	Verbal memory test (child listens to some words then repeats the ones remembered) Verbal memory delayed recall test (the series of words said are repeated after 20 min) Verbal memory essay of Recognition test (words are read out loud and respondents identifies those that were in the previous list) Visual memory (series of images are presented after which respondents verbalizes those remembered) Visual memory delayed essay (the images remembered are said out loud after 20 min) Visual memory essay of recognition (respondent identifies if images presented were in previous list)	Memory	Verbal memory: verbal list learning—VLL (two lists of 15 items are read out to the child as a shopping list. The first is presented five times and the second only once)
Language	Verbal comprehension images test (respondent matches images to given conditions) Verbal comprehension figures (respondent matches geographic shapes to given conditions) Phonetic fluency (a letter is presented and respondents verbalizes all words that start with the letter given)	–	–
Executive functioning	Working memory (a list of color and numbers are said and respondent repeats the numbers then the colors) Abstract reasoning (respondent completes a logical series by selecting the right element) Semantic fluency (a category is given and respondents says the elements known in that category) Inhibition: Go/NO-GO (respondents identifies distinguishing factor between two elements and later identify the distinguishing element) Flexibility: spatial stroop (respondent matches arrow directions to arrow labels) (two components of spatial stroop—attention shifting task measures flexibility while proper spatial stroop task measures inhibition) Flexibility: alternate visuo-motor (is flexibility measure that involves two distinct series in which the respondent should connect alternatively) Planning: attraction park (respondent chooses a number of attractions according to money in hand with each attraction chosen expiring after a given period)	Executive functioning	Working memory: dots (a sheet of eight designs made of dots. The examiner identifies the “special” dot in each design, from a series of one up to eight. The subject is required to point at the special dot. Three trials are administered at each level as required) Reasoning: colored progressive matrices—CPM (three sets with 12 matrices made of abstract patterns. The subject is asked to complete the matrix by placing one of a choice of four patterns in the empty space) Attention and attention shift: contingency naming test—CNT (the child is taught a series of rules to name nine drawings displayed in a single series. Each drawing consists of a large outer colored shape and a smaller inner colored shape. Each drawing is named according to the shape or color of one of its two shapes. The rules taught for selecting the name of the item become more complex over four trials) Planning: tower test (three colored wooden balls are moved between three pegs to match a goal position. Time and number of moves required are recorded)

The units of measurement in the BENCI and Kilifi Toolkit are reaction time (RA), total number of correct answers (CA) and number of moves. Measurement in KABC II is through the Fluid Crystallized Index

**Fig. 1 Fig1:**
[figure not shown]
Sub-tests screenshots

The Kilifi Neuropsychological Tool Kit comprises of a set of measures adapted and standardized from published measures. The tools have good psychometric properties with split half reliability being between .70 and .84 while internal consistency was ≥ .70 [10]. Some of the cognitive domains they cover include executive functioning, memory and attention. The reliability of the assessment tools is tested among children aged 8–11 years; hence the tools have norms befitting this age group. The measures are all paper and pencil based. These measures are administered to allow for comparison in performance in a paper–pencil test vs. a computerized battery. The tools can be administered within 120 min. See Table 1 for the assessment tools within the two tests.

#### Procedure for translation measures and data collection

The Guidelines for Translating and Adapting Tests developed by the International Test Commission will be used in adapting and standardizing the tool [11]. Permission will first be sought from the developers of the BENCI for modification of the tool. The test developers will also be involved in the modification in ensuring the modifications suggested do not in compromise the validity of the tool. Also, in ensuring the changes are integrated in the computerized version of the tool. Since the BENCI is originally in Spanish, two bilingual translators, one whose native language is Spanish and the other whose native language is English, will be involved in translating the battery. One will translate the tools from Spanish to English and the other check for linguistic and cultural consistency of the English version. Clinical psychologists and psychiatrists, who will be part of the data collection team, will form the third team that will check for synthesis. At this stage the culturally adapted version will be assessed and evaluated against the tool’s original markers. This is where cultural references in the Spanish version that are unfamiliar within the Kenyan children setting will be identified and identical but familiar references integrated. The tool’s structure and appropriateness (such as grammatical correctness) will then be evaluated. A word for word literal translation from Spanish to English may result in grammar and format errors. To curtail such structural problems, the translators as well as the investigators will check the appropriateness of the translated version while maintaining the characteristics of the original test. We will aim for conceptual translations as opposed to literal translations.

A pretest of the BENCI will be carried out in order to identify elements that may not be well understood by respondents and problems that may be encountered during the main study. The piloting will be carried out among randomly selected 10 children from a community-based HIV programme. The randomization will be carried out among 8- to 10-year-old who are living with HIV. They will be randomly selected as they come into the clinic for their usual appointments and requested to enroll for the pilot study. The piloting will aid in adapting BENCI in terms of modifying item formats that may not be recognized by respondents, eliminating translation bias among other modifications. In order to improve content validity, inter-rater reliability analysis will be carried out where two raters will review the results of the pretest. One rater will administer the tool amongst the pilot sample, while the other rater will review how the tool is administered and the respondent responds. This work will be qualitative in nature trying to identify and refine the items and their relevance within BENCI.

HIV exposed and unexposed children will be considered as comparative groups—and potentially matched on the patient background characteristics (age and gender). The two comparable groups will be of equal sample sizes which will be calculated using a formula cited in Wittes [12].

In this study sample size computation is based on data from earlier studies in Africa, the $$ \mu_{1} = 184.7 \left( {sd = 63.7} \right)\;{\text{and}}\;\mu_{2} = 200.6 \left( {sd = 68.7} \right) $$ which are derived using KABC-2 between HIV exposed and unexposed [13]. Thus, the assumed pooled standard deviation of the mean difference is approximately (sqrt (68.7^2^ + 63.7^2^)/2) = 66.3. Together with a significance level of 5% and a power of 80%, these result in a total sample size of 544 respondents, 272 in each study arm. So, the study will need to enroll 272 HIV exposed children and 272 unexposed children.

Respondents will be recruited using random stratified sampling by sex and age. A list of all respondents aged 8–11 years in the HIV program and 8–11 years in the primary schools according to gender will then be extracted from the children data base in the institutions. The children’s caregivers will then be requested to give consent on behalf of the children in the schools and the HIV program. A list of all the children with parental consent will then be compiled in readiness for data collection day. On data collection day, the respondents who agree to participate, will be shown the room with neuropsychological assessment tools and proceed with the demographic questionnaire and later on the neuropsychological tests. The process will take around 90–120 min per child.

### Data analysis and presentation

Since the data generated by the BENCI will be collected in computerized format, it will automatically be numerically coded with identifiers attached to different respondents and excel sheets will be generated as programmed in the tool. The Kilifi Toolkit subsets data will be manually keyed into Excel sheets after being numerically coded with identifiers that are attached to differentiate the respondents. Descriptive statistics, as well as, frequency distributions will be used to analyze the demographic traits among other characteristics of the HIV uninfected unexposed (control) and HIV infected (experimental) with the aid of SPSS. Intraclass correlation, in the same software, will be used to calculate test–retest reliability. To examine convergent validity, the raw scores of BENCI subtests will be compared to the raw scores of the subtests in Kilifi Toolkit. A confirmatory factor analysis will be used to assess construct validity. The validity indicators will be several alternative fit statistics as recommended by Hu and Bentler [14]: Chi square its degrees of freedom and its significance value (a good fitting model would show a non-significant value); root mean square error of approximation—RMSEA whose cut off is .06 and below; as well as scoring .95 and above in Comparative Fit Index (CFI) and Tucker–Lewis Index (TLI) [14]. Discriminant validity will be assessed by comparing the neurocognitive scores of the control (HIV unexposed uninfected) to the experimental group (HIV infected) as well as checking on the age sensitivity. This will be assessed using Receiver Operating Characteristics (ROC), where area under the curve will indicate the diagnostic accuracy of BENCI i.e. the ability of the BENCI to correctly classify those with neurocognitive deficits from those without. These statistical calculations will be carried out in SPSS and the diagnostic accuracy indicators will be excellent for .90–1; good for .80–.90; fair for .70–.80; poor for .60–.70; as well as, fail for .50–.60 [15]. Descriptive statistics including frequency tables, percentages, histograms and bar graphs will be used to show results, as well as, explain correlations between the variables. A neurocognitive profile curve will be used to show differences in cognitive outcomes between the experimental and control group.

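### Convergent validity rests on raw BENCI and Kilifi scores across ages 8–11 with no age control, so shared age variation would inflate the correlations

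*Protocol article*

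**What the plan says.** The Data analysis and presentation section of the protocol article defines the convergent-validity analysis in one sentence: "the raw scores of BENCI subtests will be compared to the raw scores of the subtests in Kilifi Toolkit". The abstract gives the type of method: "ANOVA and correlational analyses will be used to calculate discriminant, convergent and construct validity".

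The notes to Table 1 give the units of the BENCI and Kilifi scores as "reaction time (RA), total number of correct answers (CA) and number of moves", so these are unstandardised scores.

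On age, the procedure section says "Respondents will be recruited using random stratified sampling by sex and age", and the sampling frame is "A list of all respondents aged 8–11 years in the HIV program and 8–11 years in the primary schools". Age appears once in the analysis section, under discriminant validity, where the HIV group comparison is made "as well as checking on the age sensitivity".

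Table 1 sets six BENCI domains beside the Kilifi tests. Processing speed and language have dashes in both Kilifi columns. Visuo-motor coordination stands beside a self-ordered pointing test under the Kilifi label "Verbal/visual selective reminding". Sustained attention, memory and executive functioning have Kilifi tests in the same domain.

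For convergent validity the article states no significance level, no minimum correlation and no list of pairs.

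**The concern.** Between 8 and 11 years, raw scores on many cognitive tests can be expected to change with age. The plan shares that expectation, since it looks for age sensitivity as a sign that BENCI works. When two raw scores both move with age, they correlate for that reason, whether or not they measure the same ability. Stratifying by age builds the age spread into the sample. The two uses of age therefore pull against each other: the better BENCI does on age sensitivity, the more age contributes to its apparent agreement with the Kilifi tests.

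Establishing reliability and validity is the study's general objective, and the product is meant as an open-access measure for East Africa. Inflated convergent correlations would overstate how far BENCI measures what the Kilifi tests measure. The risk of misreading is greatest where the two tests in a row of Table 1 are of different constructs, because there an age-induced correlation could pass for convergence.

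**Working it through.** **Inputs from the article.** Total N = 544, 272 per group; planning means 184.7 and 200.6; SD 66.3; 5% significance; 80% power; ages 8–11.

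**Input not in the article.** The correlation of age with each raw score, r_a. It is assumed equal for both tests and varied from 0.1 to 0.6. Scores are taken as oriented so that higher means better; otherwise a reaction time paired with a count of correct answers would only change the sign.

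**1. The plan's own figure.** The difference is 200.6 − 184.7 = 15.9. With two-sided 5% and 80% power, n per group = 2 × (1.960 + 0.842)² × 66.3² / 15.9² ≈ 272.9. That rounds up to 273, or 546 in total, against the stated 544; power at 272 per group is 79.9%. The stated size is reproduced to within rounding. It was set for a difference in means, not for convergent validity.

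**2. Correlation induced by age alone.** If the tests share nothing but age, r = r_a × r_a.

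**3. Inflation of a real correlation.** With age-free (partial) correlation ρ, r_raw = ρ(1 − r_a²) + r_a². For ρ = 0.30 and r_a = 0.4: 0.30 × 0.84 + 0.16 = 0.412.

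| Assumed r_a | Induced r when ρ = 0 | Raw r when ρ = 0.30 |
|---|---|---|
| 0.2 | 0.04 | 0.328 |
| 0.3 | 0.09 | 0.363 |
| 0.4 | 0.16 | 0.412 |
| 0.5 | 0.25 | 0.475 |

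At r_a = 0.1 the induced correlation is 0.01, and at 0.6 it is 0.36.

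**4. If a 5% test were applied.** This is an illustration, since the article states no such test here. At N = 544 the two-sided critical value is 1.964/√(542 + 1.964²) = 0.084. The induced correlation reaches it when r_a = √0.084 ≈ 0.29. By the Fisher z approximation, the chance of p < 0.05 with ρ = 0 is about 6%, 15%, 56%, 96% and 100% at r_a = 0.1, 0.2, 0.3, 0.4 and 0.5. At N = 272 (one group) the critical value is 0.119, and the chances are 5%, 10%, 32%, 75% and 99%.

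**5. Effect of adjusting for age.** In simulations (4,000 runs per setting, N = 544, uniform age, ρ = 0, r_a from 0.2 to 0.5), the raw correlation was significant in about 16%, 56%, 97% and 100% of runs. The age-partial correlation was significant in 4.8% to 5.8%.

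**6. Pooling the HIV groups.** The planning effect is d = 15.9/66.3 = 0.24. With equal groups, the correlation of group with score is d/√(d² + 4) = 0.24/√4.0576 ≈ 0.119. If both tests show this effect, the induced correlation is 0.119² ≈ 0.014.

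**7. Domain count from Table 1.** Of six BENCI domains, two have no Kilifi test. A third has one listed beside it that asks for a different thing: pointing once to each picture in a set, as against connecting elements in sequence.

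**The case against.** The strongest reply is that the sentence says only that raw scores will be compared. A partial correlation can be computed from raw scores without contradicting it, and a condensed article may leave covariates and pair lists to a fuller document. Raw scores are also understandable while the English version is still being standardised. Part of this stands: the sentence does not rule out adjustment, and missing detail alone would be no finding. But naming raw scores is an explicit choice. Followed as written, in an age-stratified sample and with age assigned only to discriminant validity, it gives the inflated figure.

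Four stronger readings are tempting, and the documents do not support them:

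- **That shared age growth by itself will produce significant correlations.** This needs age correlations of about 0.29 or more with both tests at N = 544, and the article reports none. At 0.2 the chance is about 15%, and at 0.1 about 6%. The article also sets no significance criterion for convergent validity; its 5% level belongs to the sample size. Many readers would not accept an age-only correlation of 0.09 to 0.16 as convergence.
- **That mixing HIV-infected and uninfected children is a comparable source of inflation.** At the planning effect it adds about 0.014, and whether the groups differ is what the study is to find out.
- **That three domains lack any Kilifi test.** Two do. The third has a differently labelled test beside it, and Table 1 is a comparison of domains, not a declared list of validity pairs.
- **That convergence will be claimed where nothing comparable was measured.** The article makes no such claim and shows the two gaps openly. It simply does not say which subtests the comparison covers.

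**Conclusion.** The point holds in a conditional form. Comparing raw scores across ages 8–11 without age control mixes agreement between the tests with their common dependence on age, and the plan itself expects that dependence for BENCI. For assumed age correlations of 0.2 to 0.5 with both tests, the inflation is 0.04 to 0.25 when nothing else is shared, and a true 0.30 is shown as about 0.33 to 0.48. At the low end this is minor; at the high end it would change how a reader judges the instrument. The size rests on assumed, equal age correlations; if either test is nearly unrelated to age, the inflation for that pair is close to zero. It does not depend on any p-value, since the estimate itself is shifted. Same-construct comparison is available in three of the six BENCI domains as Table 1 stands. This should be corrected before analysis, but it does not threaten the design or the sample size.

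**What to change.** In Data analysis and presentation, make the correlation adjusted for age (partial correlation), or the correlation of age-standardised scores, the measure of convergent validity, reported with a 95% confidence interval for each pair. Keep the raw correlations as descriptive.

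List the same-construct pairs in advance. Table 1 supports candidates in sustained attention, verbal memory, working memory, reasoning, attention shifting and planning. State that no convergent claim is made for processing speed or language, nor for visuo-motor coordination on the strength of the self-ordered pointing test. If a minimum correlation is to count as convergence, fix it now and apply it to the age-adjusted value.

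The cost is wording and a small amount of analysis. Age is already recorded in the socio-demographic questionnaire, so no new data or children are needed. The downside is that the reported correlations will be somewhat lower and the claim will cover fewer domains.

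### Construct validity is judged by global CFA fit cut-offs alone, which do not require any test to load on its domain and do not detect domains that collapse into one factor

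*Protocol article*

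**What the plan says.** The second specific objective in the Introduction is "To evaluate the construct and criterion validity of these measures". Under Data analysis and presentation, the article states: "A confirmatory factor analysis will be used to assess construct validity". It then says what will count as evidence: "The validity indicators will be several alternative fit statistics". The criteria are:

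- chi-square: "a good fitting model would show a non-significant value"
- RMSEA: "RMSEA whose cut off is .06 and below"
- CFI and TLI: "scoring .95 and above in Comparative Fit Index (CFI) and Tucker–Lewis Index (TLI"

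No criterion is given for loadings, explained variance or correlations between factors. Test–retest reliability, the comparison with the Kilifi Toolkit, and the group and ROC analyses appear in the same section as separate analyses. Nothing links them to the construct-validity conclusion. The Abstract says "ANOVA and correlational analyses will be used to calculate discriminant, convergent and construct validity", also without a criterion.

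Table 1 gives six BENCI domains. Processing speed has one test, "Simple reaction time test (a plus sign of the screen prompts the child to press a key on the keyboard fast". Visuo-motor coordination and sustained attention also have one each. Memory has six, language three and executive functioning seven.

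**The concern.** Global fit statistics measure how closely a model reproduces the observed covariances. Whether a test reflects its domain is shown by the size of its loading, and whether two domains are distinct is shown by the correlation between their factors. The stated criteria use neither quantity. A model can therefore fit well while many tests carry almost no information about their domain, or while several named domains are one ability.

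What is at stake is the conclusion on objective 2. A pass under these criteria would be read as support for the claim that the English BENCI measures the listed domains in Kenyan children, and by itself it does not support that claim.

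**Working it through.** **Inputs from the article.** The total sample is 544. Its own calculation is reproduced closely: 2 × (1.96 + 0.84)² × 66.3² / 15.9² gives about 273 per group, against 272 stated. Cut-offs are those quoted above, with the 5% level from the sample size paragraph assumed for chi-square. Table 1 gives 1 + 1 + 1 + 6 + 3 + 7 = 19 tests. The article reports no CFA result or pass rate to reproduce.

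**Assumptions not in the article.** All 544 children are analysed. Scores are normal and estimation is by maximum likelihood. Each of the 19 tests gives one score, the Table 1 domains are six correlated factors, and error is fixed at 0 for single-test domains. Real loadings are .7 or .5 and factor correlations φ are .3 or .5.

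**Degrees of freedom.** There are 19 × 20 / 2 = 190 variances and covariances. Parameters are 16 loadings and 16 error variances (multi-test domains), 3 variances (single tests) and 15 factor correlations, 50 in all. Model df = 190 − 50 = 140. Baseline df = 190 − 19 = 171.

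**Why noise fits.** The model-implied covariance of standardized tests i and j in domains a and b is λᵢ λⱼ φₐᵦ, with φ = 1 within a domain. A test unrelated to all others has covariance zero with each of them, and λᵢ = 0 reproduces this exactly. For a single-score domain, φ = 0 does the same. If all tests measure one ability, φ = 1 between domains reproduces the data. None of these cases adds misfit.

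**Simulation results**, share of studies meeting all four cut-offs (150 to 200 runs per scenario):

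| True structure | Loadings .7 | Loadings .5 |
|---|---|---|
| Sound battery | 92–93% | not run |
| 10 of 19 noise, two real tests in each multi-test domain | 93–94% | 70–85% |
| 13 of 19 noise, two real tests in each multi-test domain | 85–91% | 61–65% |
| 13 of 19 noise, all six memory tests real | 96% | 92% |
| 16 of 19 noise, three memory tests real | 94–95% | 82–87% |
| All 16 multi-test-domain tests measure one factor | 88% | not run |

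With all 19 tests noise, 40–41% passed. With every multi-test loading at .3, 73–89% passed. Monte Carlo standard error at 200 runs is √(.92 × .08 / 200) = 1.9 points near 92% and √(.65 × .35 / 200) = 3.4 points near 65%.

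**Why the rates vary.** TLI ≥ .95 requires T ≤ 140 × [1 + .05 × (T₀/171 − 1)], where T is the model chi-square and T₀ the baseline chi-square. Typical T₀ values from the simulations with φ = .3 give:

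- sound battery, T₀ = 3393: T ≤ 271.9
- 10 of 19 noise at .7, T₀ = 845: T ≤ 167.6
- 13 of 19 noise at .5, T₀ = 299: T ≤ 145.2

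Under a correct model T has mean 140 and SD √280 = 16.7. The last two limits lie 1.65 and 0.31 SD above the mean, so roughly 95% and 62% should pass, against simulated TLI rates of 94% and 65%. With all noise, T₀ is about 170. The TLI denominator, 170/171 − 1, is then almost zero and the index is unstable.

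**Counter-check: wrong domain.** With loadings of .7 and φ = .3, moving four of the 16 multi-test-domain tests to another domain gave 0% passing (median RMSEA .114, CFI .69). Moving one gave 0% (median CFI .91). With two executive tests that really belong to language, 0% passed at loadings of .7 and 45% at .3.

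**Effect of a loading criterion.** In 150 runs per scenario (real multi-test loadings .7, single tests .8 where not noise), every multi-test loading was also required to be at least .40:

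| True structure | Four cut-offs | Plus loadings ≥ .40 |
|---|---|---|
| Sound battery | 92–93% | 92–93% |
| 10 of 19 noise | 95–97% | 0% |
| 13 of 19 noise | 86–92% | 0% |
| All noise | 43% | 0% |

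**The case against.** **The article is condensed.** Loadings are routine CFA output, and thresholds may sit in a fuller document. That would answer a complaint that loadings go unmentioned. Here, however, the article names the validity indicators and fixes their cut-offs, so the point concerns a stated criterion.

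**Other analyses could expose a noise test.** Such a test would have a test–retest correlation near zero and no relation to a Kilifi counterpart. This is fair, and nothing says a CFA pass overrides those results. Equally, nothing ties them to the construct-validity conclusion. Table 1 shows no Kilifi counterpart for processing speed or language, and test–retest agreement shows stability, not which domain a test reflects.

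**The model and scenarios are assumed.** This stands. The article does not specify the factor structure or the CFA sample, and Instruments description counts 14 tests where Table 1 lists 19; a 14-test model was not simulated. Nothing suggests that most BENCI tests are noise: the Introduction reports good validity and reliability in Morocco and Ecuador. The scenarios test the criteria and do not forecast this study's result.

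**One test need not mean one score.** The note to Table 1 lists reaction time, correct answers and number of moves as units. A single-test domain might therefore enter with several scores, so the point about such domains is conditional.

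**Conclusion.** The criteria for construct validity are incomplete and should be changed. Under the assumed 19-test, six-domain model with 544 children, largely uninformative batteries meet all four cut-offs in roughly 60% to 96% of studies, against about 92% for a sound battery. Domains that are really one factor pass in 88%. The percentages depend on the assumed loadings, factor correlations and model. The mechanism does not: zero loadings and unit factor correlations are compatible with perfect fit.

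A reader might infer three stronger claims, none of which is supported:

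- **That fit is unrelated to whether tests measure their domains.** Strong tests in the wrong domain failed every time.
- **That a noise battery is certain to be declared valid, or that weaker batteries generally pass more easily.** Only about 40% of all-noise batteries passed. Correctly assigned tests with loadings of .3 passed in 73–89%, below the sound battery. Leniency appeared only for wrong assignments combined with weak loadings.
- **That the CFA can say nothing about the three single-test domains.** This holds only if each enters with one score, since loading and error variance then cannot be separated.

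**What to change.** Keep acceptable fit as a necessary condition and add two or three sentences, for example:

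*Construct validity of a domain with two or more scores is supported if model fit is acceptable, each standardized loading reaches a pre-stated minimum (for example .40), and the domain's correlations with other factors are clearly below 1. Loadings and factor correlations are reported per domain. No construct-validity claim is based on the CFA for a domain that enters with a single score.*

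For single-score domains the conclusion should rest on the other planned analyses. The plan should note that processing speed has no Kilifi counterpart, so convergent evidence from that toolkit is unavailable for it.

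The loadings and factor correlations come from the same model, so no new data are needed. The costs are that some domains may not be declared construct valid and that the loading minimum is a convention needing justification in advance. The simulations tested the loading criterion; the factor-correlation criterion is added because a collapse into one factor leaves loadings high and would not be caught otherwise.
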